### Intervention

The CEDART intervention begins at hospital admission and continues as families transition home. The intervention can be adapted over time to reflect different transition pathways among persons with dementia (e.g., hospital to home vs. hospital to nursing home to home). The types and combinations of transitional support provided (e.g., education on dementia trajectory, information on applying for social services, access to transportation service) by the community health worker are informed by prior studies, including a 2024 systematic review of 126 transitional care interventions [16]. One medical school-affiliated hospital located in Austin, Texas will be the main study site for intervention delivery and dyad enrollment.

The intervention is structured to address each hospitalized dyad’s needs through an initial assessment meeting, regular bi-weekly or weekly follow-ups, and facilitated connections to community resources. The complete intervention is designed to be delivered over three months following discharge. Figure 2 lists all intervention-related tools such as assessment and care planning forms used during each major step of the intervention process.

The intervention begins with an initial assessment conducted by the community health worker to identify primary and secondary caregiving stressors, currently utilized resources, social support, and additional needs related to social determinants of health, dementia education, care navigation, and caregiver health. This initial assessment meeting, lasting approximately 45–60 minutes, will occur either in person, via Zoom, or by telephone. It may take place during the hospital stay or within one week after discharge. The community health worker will use the initial assessment to inform the development of an individualized post-discharge care plan. They will also contact the family caregiver to review and, if needed, revise the plan to address any emerging needs or concerns. If the caregiver identifies urgent healthcare questions or requests assistance in communicating with hospital staff about patient care or discharge planning, the community health worker will facilitate communication as promptly as possible. Dyads will also receive a dementia caregiving toolkit during this meeting, which includes an individualized list of community resources.

Within the first week after discharge, the community health worker will meet with the dyad via phone or Zoom to review caregiving goals, assess additional support needs—such as care navigation and access to social services—and address any emerging concerns.

During the first month post-discharge, the community health worker will meet with the caregiver via Zoom or telephone on a weekly or bi-weekly basis to provide coaching, dementia caregiving education, and care navigation support. In the second and third months, they will conduct approximately four additional bi-weekly follow-up meetings with the caregiver. These sessions, lasting 30–45 minutes, will be conducted via telephone or Zoom. Follow-up meetings will include a brief review of the dyad’s goals and address any new questions or needs related to post-discharge care navigation. The community health worker will also continue to monitor the dyad’s well-being, offer socioemotional support, and facilitate connections to community resources as needed.

### Control group

This study will employ a single-arm feasibility design without a control group.

### Feasibility study outcomes

Primary study outcomes will be focused on feasibility, acceptability, and fidelity. Secondary study outcomes include assessing the acceptability of measurement tools administered during caregiver interviews at baseline, 6-weeks, and 12-weeks, and exploring the preliminary efficacy of the intervention.

Main outcomes for our study focus on feasibility and include:

Number of participants with dementia and caregivers screened, eligible, and enrolled.Identification of effective recruitment strategy to inform a future definitive trial.Feasibility and acceptability of the intervention, including its content, delivery, and fidelity.Completion rates of follow-up interviews and outcome measures.Reasons for non-recruitment and attrition.Acceptability of recruitment procedures, assessments, data collection tools, and intervention delivery.Baseline scores and variability of secondary outcomes to inform sample size estimates for a future trial.

### Qualitative data collection

#### Design

In addition to quantitative metrics, we will also use a qualitative descriptive approach [39, 40] to describe stakeholders’ views on the acceptability and feasibility of the CEDART intervention procedures, recruitment process, content and delivery, and data collection methods. This approach will help identify factors that facilitated or hindered study participation. Any additional feasibility issues that may emerge from data analysis will inform the design of a future randomized controlled trial. Table 3 summarizes who will be interviewed throughout the study period.

Qualitative data collection will consist of individual, semi-structured key informant interviews with diverse stakeholder groups from two hospitals, and the broader community. The interviews will occur both before and after intervention implementation to capture stakeholder insights regarding the transitional care process, identify existing challenges, and elucidate priorities for enhancing care transitions. All qualitative interviews will last approximately 30–60 minutes and will be conducted via each participant’s preferred method, including in-person, telephone, or Zoom.

### Main trial outcome measurements

To inform the design of a future definitive trial, we will evaluate the feasibility and acceptability of several secondary outcome measures. These include the Quality of Life in Alzheimer’s Disease scale [41, 42] and caregiver-reported 30- and 90-day hospital and emergency department (ED) readmissions to assess impact on persons with dementia. Caregiver-specific outcomes will be measured using the Zarit Burden Interview–4 [43], Caregiver Outcomes of Psychotherapy Evaluation [44], Family Caregiver Activation in Transitions (FCAT) [45], and indicators of post-discharge care compliance [46]. Detailed descriptions of these measures are attached [see Additional File 3]. Table 4 summarizes how feasibility study outcomes will inform a future definitive trial.

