**Methods::**

Forty hospitalized persons with dementia and their caregivers will receive the CEDART intervention. Eligible patients with confirmed or suspected dementia will be enrolled from a Texas hospital. Respective caregivers will then participate in an initial assessment meeting followed by individualized care planning and follow-up meetings led by the community health worker. The community health worker will continue to provide caregivers with tailored dementia care education, emotional support, and connections to community resources for up to three months post-discharge. Input from a community advisory board of hospital system partners, community-based service providers, and dementia care experts - alongside key informant interviews with hospital providers, community providers, and caregiver participants receiving CEDART intervention, will be used to evaluate the acceptability of the intervention. Key informant interviews will be conducted to assess whether the intervention meets and addresses stakeholder priorities. Participating caregivers will complete baseline, 6-week, and 12-week follow-up interviews to assess caregiver outcomes and intervention feasibility and acceptability.

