### Data management

All participant data will be kept strictly confidential. Qualitative interview data will be digitally recorded, transcribed, and de-identified after verification for accuracy. Quantitative data (e.g., survey responses, chart reviews) will be entered into an SPSS dataset without identifiable information. Each participant will be assigned a unique study ID, with identifiable information (e.g., name, contact details) stored separately from research data. Identifiable information will be maintained in a password-protected Microsoft Excel file on a secure server until study completion, accessible only to authorized research personnel. Protected health information from chart reviews will be stored separately from participant identifiers after data entry into a secure, password-protected database. Both electronic and physical copies of protected health information will use study IDs. Hard copies of data will be kept in locked file cabinets within a secured office. Electronic data will be stored in a password-protected database. Audio recordings will be erased after transcription.

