**Figure 2 F2:**
[figure not shown]
CEDART Intervention Process

**Table 1. T1:** Schedule of enrollment, intervention and assessments per SPIRIT 2013

	Study Period		
	Enrollment	Post Enrollment	Close Out (12 weeks)
Timepoint	-T1	T1	T2
Enrollment			
Eligibility screen	X		
Informed consent	X		
Demographics	X		
Intervention			
Community health worker-led Care Transition Support		X	
Assessments			
QoL-AD, number of hospital and emergency department admission, ZBI-4, COPE, FCAT, Post-discharge compliance	X	X	X
Acceptability interview			X

Note: QoL-AD = Quality of Life in Alzheimer's Disease; ZBI-4 = Zarit Burden Interview–4; COPE = Caregiver Outcomes of Psychotherapy Evaluation; FCAT = Family Caregiver Activation in Transitions. Post-discharge compliance refers to caregiver-reported adherence to the recommended post-hospital care plan.

**Table 2. T2:** Patient and caregiver eligibility criteria

Patient	Caregiver

Inclusion Criteria	Inclusion Criteria
1. ≥50 years of age 2. Confirmed or suspected dementia or cognitive impairment 3. Scores 4–6 on Functional Assessment Staging Tool 4. Admitted to the hospital from home 5. English- or Spanish-speaking	1. ≥18 years of age 2. English- or Spanish-speaking 3. Patient’s relative or partner 4. Provides regular, unpaid medical care and or assistance
Exclusion Criteria	Exclusion Criteria
1. Do not meet all inclusion criteria 2. Patients who are eligible for hospice	1. Do not meet all inclusion criteria

**Table 3. T3:** Qualitative data collection process

Participants	Number interviewed before the start of the study	Number interviewed at post-discharge Week 12	Number interviewed at the end of the study
Caregiver intervention participants		40	
Community health worker interventionist			1
Hospital providers	5		5
Caregivers	5		5
Community service providers and content experts	5		5

**Table 4. T4:** Summary overview of how the feasibility study may inform a future definitive trial

Pilot study	Future definitive trial
Intervention content and delivery	Finalized Intervention content and modes of delivery
Participant recruitment	Effective participant recruitment strategy established
Training requirements	Research staff and CHW training needs identified
Study protocol	Study protocol developed for all study processes
Data collection tools (quantitative & qualitative)	Final quantitative secondary outcome measurements selected, and qualitative interview guides developed

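### The caregiver-reported 90-day readmission outcome runs past the last scheduled caregiver assessment at 12 weeks (nominal day 84), so its last six days have no stated data source

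*Protocol article*

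**What the plan says.** The section Main trial outcome measurements names the outcome as "caregiver-reported 30- and 90-day hospital and emergency department (ED) readmissions to assess impact on persons with dementia". The caregiver is the only source given for it.

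The Methods part of the Abstract sets the contact times: "Participating caregivers will complete baseline, 6-week, and 12-week follow-up interviews". Objectives, Feasibility study outcomes and Quantitative analysis give the same three times. Table 1 lists the admission count with the other assessments ("QoL-AD, number of hospital and emergency department admission, ZBI-4, COPE, FCAT, Post-discharge compliance") at enrolment, post enrolment and a last column headed "Close Out (12 weeks"). No assessment column follows.

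Table 1 states no origin for the 12 weeks. Table 3 does, in a column headed "Number interviewed at post-discharge Week 12", but that table covers the qualitative interviews only.

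Two other contacts with the data could matter. The Intervention section says: "The complete intervention is designed to be delivered over three months following discharge". Data management mentions chart reviews: "Quantitative data (e.g., survey responses, chart reviews) will be entered into an SPSS dataset without identifiable information". Neither is named as a source for readmissions. Detailed descriptions of the measures are deferred to Additional File 3, which is not shown.

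**The concern.** A caregiver interviewed on day 84 cannot report an admission on day 87. If the plan is followed as written, the figure reported as a 90-day rate is an 84-day rate under another name. An event in the last six days would be recorded as no event, and no opposite error from this cause offsets it.

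The unstated origin adds to this. Dyads are enrolled while the patient is in hospital. If the 12 weeks were counted from enrolment, observed time after discharge would fall below 84 days and would vary with the remaining length of stay.

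What is at stake is comparability. There is no control group, so a reader will naturally set the rate beside 90-day rates from elsewhere. The study is also meant to settle which outcome measures the definitive trial will use, so a mismatch between outcome window and interview schedule could be carried into that trial.

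**Working it through.** The article states no readmission rate and no power calculation, so there is no figure of its own to reproduce.

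**Inputs from the article.** Outcome window 90 days; last caregiver assessment at 12 weeks; 40 dyads.

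**Inputs assumed.** True 90-day risk *p* from 10% to 60%; constant hazard after discharge; interviews held exactly on schedule; no deaths or losses to follow-up.

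**Step 1, days.** 12 × 7 = 84. 90 − 84 = 6 days unobserved, and 6/90 = 6.7% of the window.

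**Step 2, recorded risk if the 12 weeks start at discharge.** Risk seen by day *t* is 1 − (1 − *p*)^(*t*/90), with *t* = 84. Example for *p* = 0.30: 1 − 0.70^(84/90) = 0.283, a shortfall of 1.7 points, and 40 × 0.0168 = 0.67 patients.

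| True 90-day risk | Recorded at day 84 | Shortfall (points) | Patients of 40 | Chance that at least 1 of 40 is missed |
|---|---|---|---|---|
| 10% | 9.4% | 0.6 | 0.25 | 0.225 |
| 20% | 18.8% | 1.2 | 0.48 | 0.383 |
| 30% | 28.3% | 1.7 | 0.67 | 0.493 |
| 40% | 37.9% | 2.1 | 0.83 | 0.568 |
| 50% | 47.6% | 2.4 | 0.95 | 0.616 |
| 60% | 57.5% | 2.5 | 1.01 | 0.640 |

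The last column is 1 − (1 − shortfall)^40.

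**Step 3, front-loaded hazard.** With a Weibull shape of 0.7 (assumed), the exponent 84/90 becomes (84/90)^0.7. The shortfall is then 0.9, 1.5 and 1.8 points at true risks of 20%, 40% and 60%, smaller than under a constant hazard.

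**Step 4, recorded risk if the 12 weeks start at enrolment in hospital.** The interval from enrolment to discharge is not given, so two values are assumed.

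| Enrolment before discharge | Last day seen after discharge | Shortfall for *p* = 10% to 60% | Patients of 40 |
|---|---|---|---|
| 7 days | 77 | 1.4 to 5.7 points | 0.55 to 2.26 |
| 14 days | 70 | 2.1 to 9.0 points | 0.85 to 3.61 |

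**Step 5, the 30-day outcome.** The 6-week interview falls on day 42, which covers 30 days if counted from discharge, or from enrolment no more than 42 − 30 = 12 days before discharge. The 30-day part is therefore largely unaffected.

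**The case against.** The best defence is that this is loose labelling with little effect. The article may use 12 weeks, three months and 90 days for the same horizon. It states no visit window, so an interview held six or more days late would cover day 90. Additional File 3 may define the measure more exactly. The bias is also small beside sampling error: at a risk of 30% with 40 patients the standard error is √(0.30 × 0.70/40) = 7.2 points, about four times the 1.7-point shortfall. All of this limits the size of the point. It does not remove the mismatch, because the article names a 90-day window, a single source and a schedule for that source that stops at 12 weeks.

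Four stronger readings are tempting, and the document does not support them:

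- **That every patient's outcome is understated.** Only a patient whose first event falls after the last interview and by day 90 is misclassified (for a count, a patient with any event in those days). All others are recorded correctly.
- **That the 90-day window can never be observed.** This would require every interview to fall on or before its nominal day, which the article does not say.
- **That Table 1 counts from enrolment and so contradicts Table 3.** Its Enrollment and Post Enrollment headings name periods, not an origin. Both tables place the acceptability interview at week 12, and they are compatible if close-out is post-discharge week 12. What can be said is that no origin is stated for the outcome interviews.
- **That the planning of the definitive trial is compromised.** Table 5 bases its sample size estimates on QoL-AD, COPE and ZBI-4, and no progression criterion names a readmission rate.

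**Conclusion.** The point stands as a minor one. A caregiver-reported 90-day outcome does not fit a last caregiver assessment at nominal day 84, and nothing in the article names a source for the remaining six days.

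If the 12 weeks run from discharge, the rate is too low by about 0.6 to 2.5 points, at most about one patient of 40, and in many realisations nobody is misclassified. These sizes rest on the assumed risks and the constant hazard; a front-loaded hazard makes them smaller. The larger figures for an enrolment origin are conditional on a reading that the article leaves open and on assumed intervals before discharge. The direction of the truncation does not depend on these assumptions.

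Severity is low because this is an exploratory secondary outcome in a single-arm pilot that plans no inferential statements. It still merits correction, since a wrongly labelled window is easily avoided and the pilot exists partly to test such measures.

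**What to change.** State index discharge as the origin for the 6- and 12-week outcome interviews, in Table 1 and in the text. Rename the outcome as 30-day and 12-week (84-day) hospital readmission or ED visit. This is a change of wording only and remains possible even if recruitment, planned to end in May 2025, has closed. If interviews already held were timed from enrolment, report the post-discharge days actually covered, since an 84-day label would then have the same fault.

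If a 90-day figure is kept, take the readmission report at or after post-discharge day 90 for dyads still in follow-up.

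Costs: an 84-day figure is less standard than a 90-day one. Moving the contact partway would give earlier and later dyads different windows and, if the whole interview moved, would also shift the other outcomes collected at it. Renaming is the cheaper route.

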### Adverse events

For this study, an adverse event (AE) is any unexpected occurrence that risks participants’ safety, well-being, or confidentiality. Given the study’s focus on interviews, surveys, and a psychosocial intervention for caregivers of persons with dementia, AEs may include:

Psychological or Emotional Distress: Significant distress triggered by study participation.Breach of Confidentiality: Unintended disclosure of participant information.Participant Complaints or Concerns: Reports of coercion, dissatisfaction, or procedural issues.Intervention-Related Issues: Increased stress, burden, or unintended negative consequences from interacting with the community health worker.Safety Concerns: Signs of self-harm, harm to others, or elder abuse requiring mandated reporting.

All AEs will be documented and assessed by the study team. Participants experiencing distress will be offered support, with the option to pause or withdraw. If further intervention is needed (e.g., suspected abuse or severe psychological distress), appropriate reporting and referral protocols will be followed.

### Sample size

As this is a single-arm pilot study, a power analysis was not required. It is suggested that sample sizes for pilot studies be determined based on practical factors such as participant availability, budget constraints, and the number of participants required to sufficiently assess feasibility outcomes [47]. Based on these considerations, a target sample size of 40 caregiver-patient dyads was selected. This sample size accounts for the estimated number of weekly admissions of patients with dementia at the recruiting hospital and the anticipated recruitment timeline.

### Recruitment

Research team members and the main recruitment hospital site providers (e.g., hospitalists, resident physicians, case managers) will conduct initial screenings of potentially eligible patients by reviewing electronic medical record multiple times per week. Given that the Functional Assessment Staging Tool scale is not routinely documented at the hospital, patients with medical record findings clearly indicating a Functional Assessment Staging Tool score above six (e.g., loss of verbal response, independent walking, or smiling not due to another medical condition) will be deemed ineligible [32]. If no such findings are documented, research assistants will administer the Functional Assessment Staging Tool scale to caregivers for eligibility determination.

For enrollment, hospital clinical providers (e.g., primary care, palliative care, and case management teams) may introduce the study to eligible caregivers or caregiver-patient dyads. If interested, the provider will notify the research team, who will then contact the caregiver to schedule an in-person or virtual meeting to review study details, confirm eligibility, and obtain consent. If a clinical provider does not introduce the study to the caregiver, the research team may reach out via phone call or in-person visit to introduce the study following confirmation from the case management team that the family may be a good fit. The research team will:

Confirm eligibility.Obtain caregiver consent.Seek caregiver permission to contact the patient for consent/assent.Assess the patient’s capacity to consent/assent and obtain consent or proxy consent as needed.

Recruitment of clinical providers and hospital staff for interviews will occur via word-of-mouth, email, and snowball sampling. The research team will collaborate with administrative and clinical leadership to share study information with relevant staff (e.g., case managers, social workers, palliative care, and primary medical team) through emails, internal hospital communications, and team meetings. Study details will also be disseminated via a study flyer.

Stakeholder recruitment for key informant interviews will follow a similar approach, leveraging professional networks, service provider referrals, and internet searches. Caregivers for persons with dementia screened for participation in the intervention who do not meet eligibility criteria may also be considered for recruitment as key stakeholders should they express desire to contribute to the study in another way. Potential participants will be contacted via email or phone, and those expressing interest will receive further study details before providing consent. Snowball sampling will be used to expand recruitment by encouraging participants to refer colleagues. To promote participant retention, all participating family caregivers will receive monetary compensation (up to $90USD) based on intervention completeness.

